### Intervention

The READ intervention has been manualised to provide guidance on implementation for the sites, which includes suggestions on how to adapt the training to make the content suitable for each site’s resources and culture. The manual also includes a section on preparation and practical considerations to aid with implementing the study. It attempts to address the reduced resources in some of the sites by suggesting that sites in the same country share resources where possible, and if necessary. The sites also have the option to correspond with each other to share strategies to facilitate implementation.

READ training will be provided to students in small groups according to local teaching arrangements. Students will be able to feed back after the role play and to ask questions of the trainers.

The first session is delivered over 1.5 h near the start of the psychiatry rotation in each medical school; the second session, lasting 1 h, takes place later before the end of the rotation. The length of the psychiatry rotation varies in each medical school, however we advised at least 1 week elapses between the two sessions. This will allow time for students to identify examples of discrimination to discuss in the second session. The training is designed to also help the students interact more effectively with patients they meet during the psychiatry rotation. Therefore it is intended to enhance their overall learning and provide a useful experience rather than add unnecessarily to workload.

The first session includes:a personal account by an expert by experience of their illness and recovery;a structured presentation, co-delivered by the psychiatrist and expert by experience, on stigma and its impact on people with mental health problems;one or two video clips of a service user testimony. Some examples of video clips with different styles have been sent to participating sites, so that sites can then find and use appropriate clips, allowing for differences in culture and language;Two role plays by the students, one of each of experienced and anticipated discrimination;At the end of the first session students are provided with an assignment: to describe specific situations they encounter during their psychiatric rotations of anticipated or experienced discrimination reported by service users. The descriptions will then be discussed and reflected upon during the second session.

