### Control arm

A control arm is important for two reasons. First, to control for any effect of psychiatry training that occurs between the first and second sessions; second, to control for the possible effect of the baseline measures (see below). The control group will therefore be administered all the measures at the same times as the intervention group, i.e. at two sessions during which the intervention group is receiving the training. Alternatively, two separate, consecutive psychiatry rotations may act as the intervention and control groups, if this is feasible. Students will be allocated by the trainer to either the control or the intervention group according to their usual local teaching group allocation at each site.

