### Statistical analysis

Total scores for MAKS, MICA2 and the OSCE will be calculated so that a higher total score represents a more favourable outcome. Descriptive summaries of score changes will be calculated between the baseline and follow up time points for each group. Parametric and non-parametric tests will be employed to detect statistically significant differences in means on individual-level data before and after implementation of the intervention compared to the controls. Statistical analyses of individual-level data will be conducted using a random effects model accounting for clustering within sites and countries, to take into account the between country and culture variation in the attitudes towards mental illness. Changes in each outcome will be investigated at baseline and at the follow up time point after the intervention. All models will be adjusted for gender; age (as a continuous variable); country income category (high, middle or low) and familiarity with people with mental health problems (self or other i.e. family member, friend). In order to appropriately quantify the direct and indirect effects of empathy and anxiety on the three outcomes (MAKS, MICA2 and the OSCE), we will conduct a mediation analysis under the causal framework with the use of the g-computation formula, which has been shown to produce reliable estimates in such scenarios (http://aje.oxfordjournals.org/content/early/2014/12/10/aje.kwu239.full.pdf).

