## Discussion

This study applies components found to be effective from medical education research in an anti- stigma training intervention for medical students. It incorporates reflection and self reflection, which has been effective in consolidating learning and improving attitudes in medical education studies [15]. This is particularly relevant as the intervention aims to change attitudes in medical students towards patients with mental illness. The OSCE involves communication and interviewing skills training, and previous work in medical education demonstrated good communication skills lead to greater satisfaction with care in patients [41] In addition studies have shown a decrease in patients’ distress and potential susceptibility to symptoms of depression or anxiety, in response to good interviewing skills [42]. Therefore training students in interviewing skills should lead to patients feeling more able to express concerns regarding anticipated and experienced discrimination in clinical consultations.

This is also the first international study across high, middle and low-income countries, which will evaluate the effectiveness of training for medical students to respond to experienced and anticipated discrimination. The range of sites will provide a valuable contribution to test the feasibility and effect of the training in multiple settings, therefore increasing the validity of any relevant conclusions drawn from the results. In addition this study measures change in skills at addressing discrimination using an OSCE, which is a new contribution to the field of stigma research. Previous studies have mostly focused on measuring change in knowledge and attitudes [11, 12].

As the study is unfunded there is a risk some sites may drop out. In this event we will ask the remaining sites to increase their sample numbers if possible, to achieve the target sample size. Several sites (including the UK) have resources available to do so.

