Another possible limitation of the study is self-selection bias – i.e. students who already have less stigmatising attitudes and behaviour may be more likely to participate in the study, and may wish to be in the intervention group. Sites will therefore assign medical students using existing teaching groups to either the intervention or control group. To encourage control students to still attend and to minimise drop out rates, the OSCE examiner will provide oral feedback at the end of the second OSCE, which students may find useful for their general medical training and their future examinations [29].

The results of this study will help medical schools in high, middle and low income countries to implement manualised training to enable future doctors to reduce the effects of mental illness related discrimination on their patients.

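### Arms are assigned by teaching group within site, but the planned model accounts for clustering only by site and country

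*Protocol article*

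**What the plan says.** Under Control arm, the trainer places students in "either the control or the intervention group according to their usual local teaching group allocation at each site". The same section allows an alternative, if feasible, in which "two separate, consecutive psychiatry rotations may act as the intervention and control groups". The Discussion repeats the rule as a guard against self-selection: "Sites will therefore assign medical students using existing teaching groups to either the intervention or control group". Under Intervention, "READ training will be provided to students in small groups according to local teaching arrangements". Allocation and delivery are therefore both by group, and each site contributes to both arms.

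Under Statistical analysis, the main analysis is "conducted using a random effects model accounting for clustering within sites and countries". The reason given is that attitudes to mental illness differ between countries and cultures. The Abstract names only sites as the clustering level. The same section adds: "Parametric and non-parametric tests will be employed to detect statistically significant differences in means on individual-level data". Nowhere does the article mention a teaching-group or rotation-cohort effect, a cluster-robust variance, a design effect or an ICC.

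**The concern.** An analysis has to allow for correlation at the level where treatment is assigned. Here that level is the teaching group or rotation cohort, one step below the lowest level named in the model. Students in one group attend the same sessions, hear the same personal account, watch each other's role plays and join one discussion. The groups also existed before the study and were not formed by randomisation. Some correlation within groups is therefore likely, although the article does not quantify it.

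If that correlation is left out, the model treats between-group variation as independent variation between students. Confidence intervals for the READ effect are then too narrow, and an ineffective programme is declared effective more often than the nominal 5%.

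**Working it through.** **Inputs from the article.** 25 sites with on average 36 students each (Sample size), so about 18 per arm per site if split equally. Model levels: site and country (Statistical analysis). There is no stated clustering figure to reproduce.

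**Assumptions.** Teaching-group size *m* of 6, 9 or 18 (18 means one group per arm per site). Teaching-group ICC ρ of 0.01 to 0.10, on the scale on which the arms are compared. Random effects taken as intercepts.

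**Why site and country intercepts do not help.** Write a student's outcome as site effect + group effect + student error, with variances σs², σg² and σe². Within a site, the READ-minus-control difference cancels the site effect, and the country effect with it. With S sites and G groups of *m* per arm per site:

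- true variance of the arm difference = 2(σe² + mσg²)/(SGm)
- variance reported by a site-intercept model ≈ 2(σe² + σg²)/(SGm)

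With ρ = σg²/(σg² + σe²), the ratio of true to reported standard error is √(1 + (m − 1)ρ). The actual two-sided type I error at nominal 5% is 2[1 − Φ(1.96/ratio)].

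| Group size | ρ = 0.01 | ρ = 0.02 | ρ = 0.05 | ρ = 0.10 |
|---|---|---|---|---|
| 6 | 1.02; 5.6% | 1.05; 6.2% | 1.12; 8.0% | 1.22; 11.0% |
| 9 | 1.04; 5.9% | 1.08; 6.9% | 1.18; 9.8% | 1.34; 14.4% |
| 18 | 1.08; 7.0% | 1.16; 9.0% | 1.36; 15.0% | 1.64; 23.3% |

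(Each cell: ratio of true to reported standard error; type I error.) Example for 18 and 0.05: √(1 + 17 × 0.05) = √1.85 = 1.36; 1.96/1.36 = 1.44; two-sided tail 15.0%.

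**Check by simulation.** A REML model with a site intercept only was fitted to data with a teaching-group effect: 25 sites, 18 students per arm per site, site ICC 0.05, 400 runs per setting.

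| Setting | ρ = 0 | ρ = 0.02 | ρ = 0.05 | ρ = 0.10 |
|---|---|---|---|---|
| One group of 18 per arm | 3.0% | 7.5% | 12.8% | 22.8% |
| Two groups of 9 per arm | 6.5% | 10.2% | 11.7% | 15.0% |

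With 400 runs the simulation error is about 1 to 2 percentage points (for example √(0.05 × 0.95/400) = 1.1 points), so individual cells are rough. A separate simulation with 6,000 runs per setting and 16 students per arm per site gave 8.7%, 14.2% and 22.5% for one group per arm at ρ = 0.02, 0.05 and 0.10. The formula with m = 16 gives 8.6%, 13.8% and 21.5%.

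**The individual-level tests.** A plain two-sample test reports a variance proportional to σs² + σg² + σe², whereas the true one is proportional to σe² + mσg². Its standard error is too small only if (m − 1)σg² exceeds σs². With total variance 1, m = 18 and site variance 0.20:

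- group variance 0.02: 17 × 0.02 = 0.34 > 0.20; ratio √(0.78 + 0.36) = 1.07, slightly too small (simulated type I error 5.2%, against 10.0% for the site-intercept model on the same data)
- group variance 0.01: 17 × 0.01 = 0.17 < 0.20; ratio √(0.79 + 0.18) = 0.98, slightly too large

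**The case against.** The strongest objection is that the article does not say the random effects are intercepts only. A random arm effect by site would also fit its wording, and where a site has one group per arm that is exactly the missing term. An article may leave such detail to the analysis plan. This stands as a condition on the result. It does not remove the point: the article names its clustering levels, explains them by differences between countries and cultures in attitudes, which describes intercepts, and leaves out the unit by which arms are assigned.

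It is also fair that neither the ICC nor the group size is given, and that teaching is described as being in small groups. The 23% figure needs both the largest group and the highest ICC considered.

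Some stronger readings are tempting but not supported:

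- **Power is lost.** A reader might infer this from the absence of a design effect. For the stated 1.91-point change with SD 2.89, 448 per group less 10% leaves 403. At ICC 0.10 and groups of 18 the design effect is 1 + 17 × 0.10 = 2.7, so the effective size is about 149 per arm and power is still above 99.9%.
- **The large sample already allows for clustering.** The stated inputs need only 55 per group at two-sided 5% (49 before dropout). However, 448 results if 0.66 is entered as a raw difference with SD 2.89: 2 × (2.89 × 3.2415/0.66)² = 402.9, so 403, and 403/0.9 = 447.8. That route contains no design effect. In any case, more students do not correct the standard error of a model that omits the allocation unit.
- **Replacing lost sites makes it worse.** The Discussion says "we will ask the remaining sites to increase their sample numbers if possible, to achieve the target sample size". It does not say that groups would be enlarged; more students could mean more groups.
- **Groups share OSCE examiners and simulated patients.** The article does not say so, and the point does not need it.
- **The individual-level tests are always too liberal.** As shown above, they can err either way.

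**Conclusion.** The point holds. Arms are assigned by teaching group or rotation cohort within site, and the stated model stops at site and country. With site and country intercepts, the standard error of the READ effect is too small and type I error is above 5% whenever the teaching-group ICC exceeds zero.

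The size is unknown from the article. Over assumed ICCs of 0.01 to 0.10, type I error is about 6–11% for groups of 6, 6–14% for groups of 9, and 7–23% for one group of 18 per arm per site. These figures assume balanced arms within sites and equal group sizes. The harm is false-positive findings and intervals that are too narrow, not loss of power for the stated effect. The individual-level tests also do not respect the allocation unit, but the direction of their error depends on the balance of site and group variance.

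**What to change.** - In Statistical analysis, add a random effect for teaching group (or rotation cohort, where rotations form the arms) nested in site. Where a site has one group per arm, this is a site-by-arm random effect.
- Base the degrees of freedom for the READ effect on the number of groups, for example by Kenward-Roger or Satterthwaite.
- Make sure that the site database holds a teaching-group or rotation identifier for every student. The article does not list the database fields, so it may already be there. If it is not captured at data entry, it may not be recoverable later.
- Label the individual-level parametric and non-parametric tests as descriptive, or make them cluster-adjusted, for example by running them on teaching-group means.

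The cost is at most one extra database column and a change of model wording. Confidence intervals for the READ effect will be wider, because they will then reflect variation between teaching groups.

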## Methods/design

This is a multisite, non-randomised controlled study. The sites are 25 medical schools in 15 countries, including low, middle and high income countries, as outlined in Table 1 below. Sites were recruited via previous contact within the INDIGO Network (a collaboration of researchers in different countries co-ordinated by the Centre for Global Mental Health, King’s College London) or personal invitation to researchers interested in challenging stigma in healthcare professionals.

**Table 1 Tab1:** Distribution of medical schools

	Continent	Country	Number of sites
	Europe	UK	3
		Czech Republic	1
		France	2
		Spain	3
		Italy	2
		Portugal	3
		Hungary	1
		Turkey	1
	Asia	India	2
		Japan	1
		Taiwan	1
		China	1
	Africa	South Africa	1
		Nigeria	2
		Tunisia	1
Summary	3	15	25

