### Procedure for participants and data collection

Once written informed consent has been received, participating students in the intervention group will be given the questionnaire based measures to complete, and will then undertake the OSCE at the start of Session 1. Data collection using the questionnaire based measures and the OSCE will be repeated at the end of Session 2. Students in the control groups will be given the same measures and will carry out the OSCE during the same time frame as the intervention group. Instead of receiving the intervention they will be able to discuss the OSCE feedback with the role player, after the second attempt (Fig. 1).

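### The covariate list fixed for all models omits the outcome's own baseline score, so the planned change analysis is less precise than it need be and is exposed to regression to the mean if the arms start apart

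*Protocol article*

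**What the plan says.** The Statistical analysis section of the protocol article brings baseline into the analysis as part of a change. It plans descriptive summaries ("Descriptive summaries of score changes will be calculated between the baseline and follow up time points for each group") and tests of "differences in means on individual-level data before and after implementation of the intervention compared to the controls". For the random effects models, which account for site and country, it says "Changes in each outcome will be investigated at baseline and at the follow up time point after the intervention". It then fixes the adjustment set: "All models will be adjusted for gender; age (as a continuous variable); country income category (high, middle or low) and familiarity" with mental health problems, in oneself or in others. No baseline score of MAKS, MICA2 or the OSCE is in that set.

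The baseline scores exist in both arms by design. Under Procedure for participants and data collection, intervention students "will be given the questionnaire based measures to complete, and will then undertake the OSCE at the start of Session 1". Under Control arm, "The control group will therefore be administered all the measures at the same times as the intervention group". The Data management section links each student's two records by a study number.

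On design, the Methods section states "This is a multisite, non-randomised controlled study", and the Control arm section adds "Students will be allocated by the trainer to either the control or the intervention group according to their usual local teaching group allocation".

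**The concern.** When arms are formed from existing teaching groups, they may start at different levels. The direct measure of a student's starting level is the baseline score on the same instrument. The listed covariates stand in for it only indirectly, and country income category is the same for every student at a site, so it cannot account for a difference between two arms at that site.

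Two things are at stake. The first is precision: subtracting the baseline in full, as a change score does, adds noise whenever the two scores are less than perfectly correlated. The second is bias: if one arm starts higher partly by chance, its scores tend to drift back, and a change score counts that drift as a treatment effect. The same list governs all three outcomes, so the precision loss applies to each of them. The bias arises only where the arms differ at baseline and the difference does not persist.

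**Working it through.** **Inputs.** From the Sample size section: MAKS effect 1.91, SD 2.89, 448 per group, 10% dropout. Completers per arm: 448 x 0.9 = 403. The documents give no pre-post correlation r, so a range of 0.2 to 0.8 is used. Equal SDs at both time points are assumed, and clustering is ignored.

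**The plan's own figures.** The stated effect size reproduces: 1.91 / 2.89 = 0.66. The 448 per group does not follow from the printed inputs alone. At an assumed two-sided 5% level they give 49 per arm, or 55 after dropout. An allowance for clustering may sit in the full protocol. That is a separate matter and does not bear on this point.

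**Precision.** Relative to the variance of a single score:

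- change score: 2(1-r)
- follow-up score adjusted for baseline: 1-r²
- ratio, adjusted to change: (1-r²) / [2(1-r)] = (1+r)/2
- reduction from adjusting: 1 - (1+r)/2 = (1-r)/2, which is positive for every r below 1

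The standard error of the arm difference in MAKS points is 2.89 x sqrt(2v/403), where v is the variance factor.

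| r (assumed) | v, change | v, adjusted | Variance reduction | SE, change | SE, adjusted |
|---|---|---|---|---|---|
| 0.2 | 1.60 | 0.96 | 40% | 0.258 | 0.199 |
| 0.4 | 1.20 | 0.84 | 30% | 0.223 | 0.187 |
| 0.5 | 1.00 | 0.75 | 25% | 0.204 | 0.176 |
| 0.6 | 0.80 | 0.64 | 20% | 0.182 | 0.163 |
| 0.7 | 0.60 | 0.51 | 15% | 0.158 | 0.145 |
| 0.8 | 0.40 | 0.36 | 10% | 0.129 | 0.122 |

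**Bias.** Let D be the baseline gap, intervention minus control.

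- *Gap regresses to the mean.* Without treatment, the gap at follow-up would be about rD. The change score is then off by rD - D = -(1-r)D. The baseline-adjusted estimate is about unbiased.
- *Gap is stable.* Without treatment, the gap at follow-up would still be D. The change score has no bias. The baseline-adjusted estimate is off by D - rD = (1-r)D.

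The two estimates therefore differ by about (1-r)D whichever case holds. As an illustration, take an assumed D of 0.2 SD, which is 0.2 x 2.89 = 0.58 MAKS points:

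| r (assumed) | (1-r)D in SD | In MAKS points | Share of 1.91 |
|---|---|---|---|
| 0.4 | 0.12 | 0.35 | 18% |
| 0.5 | 0.10 | 0.29 | 15% |
| 0.6 | 0.08 | 0.23 | 12% |
| 0.7 | 0.06 | 0.17 | 9% |

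These figures scale in proportion to D.

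**The case against.** The strongest reply is that baseline is already used. The plan compares change with controls, and a change score removes any gap between arms that persists over time. In non-randomised groups, choosing between change and baseline adjustment is a known judgement: if the gap is stable, the change score is right and the adjusted model carries the (1-r)D error. This stands, and it is why the change model should be kept alongside. It does not defeat the point. The Discussion explains that existing teaching groups are used so that students do not select their own arm. Baseline gaps are then plausibly largely incidental, the kind that regress to the mean, although the documents cannot prove this.

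A second reply is that precision will not decide the result. For MAKS at the planned effect this is fair: with clustering ignored, even the largest standard error in the table puts 1.91 more than seven standard errors from zero (1.91 / 0.258 = 7.4). That figure covers MAKS only. The Sample size section makes no calculation for MICA2 or the OSCE, and sample size does not cure bias.

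A third reply is that an article may leave the model form to a fuller document. That is also fair, and silence on the form is not counted here. The covariate list, however, is something the article does fix, and it fixes it for all models.

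Two stronger readings are tempting. A reader might infer that only follow-up scores are compared, so that a baseline gap enters the effect uncorrected. The repeated reference to changes, in the Abstract as well as in the Statistical analysis section, points the other way. A reader might also infer that baseline and follow-up rows are stacked with no student term, so that the pairing is lost. Naming site and country effects does not exclude a student effect, and the records are linked by student.

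**Conclusion.** The point holds as a question of efficiency, with a conditional question of bias. With change as the target and the list as fixed, student-level variance is larger than it need be. Adding the baseline score would cut it by 30% to 15% for r of 0.4 to 0.7, and by 40% to 10% over 0.2 to 0.8. These figures assume equal SDs and ignore clustering. They describe student-level variation only, so the gain in the full model may differ.

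The bias of about -(1-r)D arises only if the arms differ at baseline and the gap regresses to the mean. A reader might infer from the omission that all three outcomes will be biased. The documents do not support that: they give neither D nor r, and a stable gap leaves the change score unbiased. Baseline adjustment is the better main model here because the gaps are plausibly incidental and the precision gain is nearly free, not because it is less biased in every case.

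**What to change.** Add the outcome's own baseline score to the listed covariates. For each of MAKS, MICA2 and the OSCE, take the follow-up score as the outcome, with arm, the same measure's baseline score and the covariates already named. Keep the site and country random effects as planned, and state that the arm coefficient is the READ effect.

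Report the change-score model, or an arm-by-time model with a student effect, as a sensitivity analysis, and show the observed baseline gap between arms with it. The main model can leave about (1-r)D of bias if the gap is stable. Because the two estimates differ by about that amount, the comparison would show how much depends on the choice.

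The cost is one covariate that both arms already provide, a sentence in the analysis section, and one extra model per outcome. No change to data collection or to the rest of the model is needed.
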